### Pharmacodynamic analysis

**D-dimer:** Descriptive statistics for D-dimer concentration in maternal blood will be presented in tabular form with mean, median, standard deviation and range (minimum and maximum) as appropriate. For each time point, comparisons across groups will be done using the analysis of variance. The PK data will be combined, and analyses may be conducted to determine a relationship between exposure and the effect on D-dimers.

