^. PK modelling of the oral administration of 4 g of TXA resulted in a plasma concentration of 10 mg/L within 15 min (data on file). If absorption was similarly rapid in pregnant women, this would strongly suggest the IM and oral routes as potential alternatives to IV use.

Recently, the Trauma-INTACT trial (ClinicalTrials.gov:
NCT03875937) assessed the PK of TXA administered intramuscularly in bleeding trauma patients
^
14
^. The study found that the time to reach therapeutic concentrations of 10 mg/L after intramuscular injection of 1 g TXA was within 15 min. Additionally, it was well tolerated with only mild injection site reactions and no serious adverse events reported. The PharmacoTXA trial (ClinicalTrials.gov:
NCT03777488) has assessed the PK of TXA administered intramuscularly or orally in healthy volunteers. An ongoing RCT called TRACES (TRAnexamic Acid to Reduce Blood Loss in Hemorrhagic CESarean Delivery) aims to assess the PK and pharmacodynamics (PD) effects of two doses of TXA (0.5 and 1 g) injected intravenously in women with an ongoing PPH after delivery
^
15
^.

Physiologic changes induced by pregnancy and childbirth
^
16
^ may alter the PK and PD properties of medicines, in particular due to the increase in renal elimination clearance and volume of distribution.

PPH can occur without warning in most women. However, some risk factors such as multiple pregnancy, macrosomia or previous PPH, are known to be associated with an increased risk of PPH
^
17,
18
^.

In this study we will assess the PK, PD, safety and efficacy of TXA administered by IV, IM or oral routes in women giving birth by caesarean section (CS) with at least one risk factor for PPH. Blood samples will be taken from the women immediately before the administration of TXA (1 hour before CS) and at different time points during 24 hours after receipt of intervention. Blood samples from the umbilical cord after clamping and from newborns (obtained from the sample taken for routine heel prick test) will be taken to measure the amount of TXA transferred from the mother to the neonate via the placenta. The efficacy of the different routes of TXA administration in preventing blood loss, reducing fibrinolytic activity, and the safety of the interventions will be evaluated.

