### Secondary objectives

•To assess the effect of the three routes of TXA administration on D-dimer concentration in blood samples.•To assess the concentration of TXA that crosses the placenta into the neonate via the three routes of administration.•To assess clearance of any TXA in neonate.•To assess the safety of the three routes of TXA administration.•To assess the effect of the three routes of TXA administration on postpartum bleeding.

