### Secondary endpoints

•Blood concentrations of D-dimer over time•TXA concentration in umbilical cord and neonate after birth•Local reactions at IM injection sites•Adverse events (maternal and neonate)•Neonate status Apgar score•Measured blood loss from start of CS to 2 hours after•Clinical diagnosis of PPH

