### Collection and storage of biological samples

Only one blood sample for PK analysis will be collected at baseline for women who are randomised to receiving no TXA. Samples for D-dimer, full blood count (FBC) and renal function will be collected.

Maternal blood will be taken from a cannula to avoid multiple venepuncture as follows:

Two samples of 3mL each will be taken for FBC and two samples of 3mL each for renal function. Blood samples will be collected in purple top EDTA tubes for FBC and yellow top tubes with separation gel and clot activator for renal function.

Five samples for D-dimer of 3 mL for each sample of blood to be taken in collection blue top tubes containing 3.2% sodium citrate. Blood samples for D-dimer, FBC, and renal function will be collected from the hospitals and analysed by a local central laboratory. The laboratory will be asked to store the sample used for D-dimer analysis until the end of trial to allow for repeat tests if needed. In the event of failure of any of the PK samples, this will be used as a back-up and will be destroyed at the end of the trial.

Each maternal PK sample require about 20 µL of blood taken using a Mitra
^®^ cartridge from a finger prick (2 × 10 µL samples taken on the 2 cartridges of the same device to have one primary and one confirmation sample if needed). Sites will be provided with written procedures on how to obtain the blood sample using the Mitra
^®^ cartridge. Cartridges will be labelled with the date and time the sample was taken and with the participant Study Identification number.

The total volume of blood taken (less than 35 mL) should have no clinical impact on the participant.

To obtain the umbilical PK blood sample, once the umbilical cord is clamped, it is wiped with antiseptic and a syringe and needle is inserted into the vein in the umbilical cord to withdraw a small amount of blood. PK samples from the umbilical cord and neonates will also be taken using the Mitra
^®^ cartridge system as described above.

A blood sample from the neonate (2×10 µL) will be taken using the Mitra
^®^ cartridge at the time of the routine clinical heel prick test to avoid additional heel pricks.

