### Efficacy

**Blood loss at 2 hours**: Descriptive statistics for maternal blood loss at 2 hours post-partum and total blood loss will be presented in tabular form with mean, median, standard deviation and range (minimum and maximum) as appropriate. Comparisons across groups will be done using the analysis of variance.

**Clinical diagnosis of PPH**: Number (%) of women in each randomised group will be presented.

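### D-dimer, an endpoint defined over time, is tested by a separate ANOVA at each time point with no stated adjustment or route-versus-no-TXA contrast; one longitudinal model would use the same data better

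*Protocol article*

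**What the plan says.** The Secondary objectives include this aim: "To assess the effect of the three routes of TXA administration on D-dimer concentration in blood samples". The matching entry under Secondary endpoints is "Blood concentrations of D-dimer over time". The description of the investigational product makes the 30 women given no TXA the control group for pharmacodynamics. Collection and storage of biological samples provides for five D-dimer samples per woman, "analysed by a local central laboratory". Blood sample analysis requires the assay within 3 hours, and the trial runs in Pakistan and Zambia.

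Pharmacodynamic analysis gives the whole D-dimer plan in three sentences:
- "Descriptive statistics for D-dimer concentration in maternal blood will be presented in tabular form with mean, median, standard deviation and range".
- "For each time point, comparisons across groups will be done using the analysis of variance".
- An optional step: PK data are combined and "analyses may be conducted to determine a relationship between exposure and the effect on D-dimers".

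Neighbouring paragraphs say more. The cord and neonate paragraph also uses ANOVA by time point, but adds an adjustment for the interval between dose and sample. Safety parameters specifies change from baseline for blood count and renal function. The D-dimer paragraph has neither.

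**The concern.** The method does not fit the question the protocol sets. The endpoint is a course over time, measured repeatedly in the same woman, but it is split into unconnected tests. The objective is the effect of each route, and a control arm exists for it. A four-group comparison asks only whether some group differs, and no route-versus-control difference is prespecified. Between-laboratory variation also stays in the error term, because samples that must be assayed within 3 hours in two countries need at least two laboratories.

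The main aim is whether IM and oral TXA reach levels that inhibit fibrinolysis, and D-dimer is the only fibrinolysis marker among the endpoints. With about 30 women per arm, an inefficient analysis could leave a real effect unclear, and several uncorrected tests could make a chance result at one time look like a finding.

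**Working it through.** **The plan's own figure.** 4 arms × 30 = 120 women. The 120 is justified by the precision of PK parameters (relative standard errors below 30%) from PFIM. The variances behind it are not given, so it cannot be recomputed. The article states no D-dimer effect, SD, alpha or power, so there is no D-dimer figure to reproduce.

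**Inputs.** From the article: n = 30 per arm, five D-dimer samples, two countries, 3-hour assay window. Assumed: two-sided alpha 0.05, a true difference of 0.5 SD, and a correlation ρ between pre-dose and post-dose D-dimer of 0.3, 0.5 or 0.7.

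**Baseline adjustment at one time point.** Residual variance is multiplied by (1 − ρ²). The standard error of a route-versus-control difference, in SD units, is √(1 − ρ²) × √(2/30). Power ≈ Φ(0.5/SE − 1.96). The difference detectable with 80% power is (1.96 + 0.84) × SE.

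| ρ | variance factor | equivalent women per arm, 30/(1 − ρ²) | detectable at 80% (SD) | power for 0.5 SD |
|---|---|---|---|---|
| unadjusted | 1 | 30 | 0.72 | 0.49 |
| 0.3 | 0.91 | 33 | 0.69 | 0.53 |
| 0.5 | 0.75 | 40 | 0.63 | 0.61 |
| 0.7 | 0.51 | 59 | 0.52 | 0.77 |

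**Cost of the four-group test itself.** With all three TXA arms shifted by 0.5 SD, the noncentrality is 30 × (0.375² + 3 × 0.125²) = 5.625. On 3 and 116 df the power is 0.475, against 0.49 for one pairwise comparison. The omnibus form therefore costs almost no power; what it lacks is a named difference with an interval.

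**Using the repeated measures.** If four post-dose values are averaged and baseline-adjusted, with common correlation ρ throughout, the variance relative to one unadjusted time point is (1 + 3ρ)/4 − ρ².
- ρ = 0.5: 0.625 − 0.25 = 0.375, against 0.75 for one adjusted time point.
- ρ = 0.7: 0.775 − 0.49 = 0.285, against 0.51.

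**Laboratory.** For two equal-sized laboratories that differ by s within-laboratory SDs, unadjusted variance is multiplied by 1 + s²/4. This is 1.06 at s = 0.5 and 1.25 at s = 1.

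**Several tests.** Under independence the chance of at least one false positive is 1 − 0.95⁴ = 0.185 over four time points and 1 − 0.95⁵ = 0.226 over five. These are upper bounds. In simulation with values in the same woman correlated 0.5 to 0.7, it is about 14% to 16% over four and 15% to 19% over five.

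**Scale, only if D-dimer were log-normal.** With all routes at 0.7 times control, simulated power of raw against log ANOVA is 0.59 v 0.64 (log SD 0.6), 0.32 v 0.39 (0.8) and 0.18 v 0.26 (1.0).

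**The case against.** The strongest reply is that this is a condensed article. Covariates, transformations, contrasts and multiplicity often sit in the full protocol or the SAP, neither of which is shown, and the text never says the ANOVA is unadjusted or on the raw scale. That stands against any point built on silence alone. It does not remove the method the article does fix: a separate comparison at each time point for an endpoint defined over time.

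It is also true that D-dimer is secondary, that the trial is sized for PK precision, that each test holds its nominal level, and that an exposure-response analysis is foreseen, though only as an option.

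A reader might infer four stronger claims that the documents do not support.
- That a pre-dose D-dimer value is known to exist and is being discarded. The Background mentions blood samples before dosing in general terms, which makes one likely. The D-dimer times are in Figure 3, which is not shown, and the pre-dose sample named under TXA administration and timing of biological samples is for PK.
- That D-dimer is skewed, so raw-scale ANOVA is wrong. No distribution is described anywhere, and the plan tabulates median and range as well as mean and SD.
- That the plan yields no estimate of a route effect. Arm means and SDs are tabulated, so differences can be derived, and ANOVA permits contrasts. None is prespecified, which is the narrower point.
- That blood loss shares the fault because its section says "Comparisons across groups will be done using the analysis of variance". The wording is similar, but blood loss is not a series over time, so the repeated-measures argument does not carry over.

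**Conclusion.** The point holds as a matter of efficiency and focus. The stated D-dimer analysis splits a longitudinal endpoint into separate valid tests, states no baseline or laboratory/country adjustment, and prespecifies no comparison of each route with the arm designated as control.

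The size of the loss cannot be read from the documents. It depends on the assumed correlation and on a pre-dose D-dimer sample having been taken: slight at ρ = 0.3 (as if 33 women per arm rather than 30) and substantial at ρ = 0.7 (59 rather than 30). The laboratory term matters less unless the laboratories differ by close to 1 SD. The 19% to 23% false-positive figure is a ceiling under independence. The primary PK analysis is untouched, so this is a change the sponsor should make rather than one the trial depends on.

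**What to change.** Replace the per-time ANOVAs for D-dimer with one longitudinal mixed model, on the log scale if the data are skewed. Include arm, time, arm-by-time, country or laboratory, and the pre-dose D-dimer value if it is collected. Use the pre-dose value as a covariate, not as a further time point to test. Report each of IV, IM and oral against no TXA with a 95% CI, and name in advance either one main time or the average over post-dose times. Descriptive tables by time point can stay.

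The cost is a change of wording and slightly more analysis work, with no new samples or visits. On the log scale the results become ratios of geometric means, which need a line of explanation. The change should be settled before the data are examined by arm.

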### Safety parameters

**Full blood count and renal function parameters:** Descriptive statistics for baseline and follow-up will be presented for each laboratory parameter. Changes from baseline as well as shift tables for laboratory parameters will be presented. All laboratory values will be classified as normal, below normal (low), or above normal (high) based on normal ranges supplied by the central laboratory. Frequencies of abnormal values will be presented in tabular form. For purposes of analyses, laboratory results based upon standardized units will be used.

**Vital signs:** Descriptive statistics for blood pressure, heart, and respiratory rate will be presented in tabular form with mean, median, standard deviation and range (minimum and maximum) as appropriate. Number (%) of women with abnormal values in each randomised group will be presented.

**Expected adverse events (collected routinely as outcomes for all participant):** For each event, the number (%) of women in each randomised group will be presented.

**Other adverse events:** Adverse events will be coded by primary system organ class and preferred term using the Medical Dictionary for Regulatory Activities (MedDRA). The number of events (n) and number (%) of participants with events will be presented. Events will be presented separately for maternal and neonates.

**IM injection skin reaction:** Number (%) of women with a reaction and severity of reaction will be presented.

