^. This review confirmed that there are no reports of adverse neonatal outcomes associated with the administration of TXA shortly before giving birth to prevent PPH
^
42
^. A systematic review on the effectiveness and safety of the use of TXA to prevent PPH that included 25 studies with a total of 4,747 participants concluded that there was no increased risk of deep vein thrombosis and an increased risk of minor transient events, i.e. nausea, vomiting, headache or dizziness
^
44
^. The included studies that evaluated the safety of TXA on neonates reported that no adverse events occurred, and the Apgar score that assesses the baby’s health immediately after birth showed no difference between babies in TXA-treated and control groups
^
44
^.

No mutagenic activity of TXA has been detected
*in vitro* and
*in vivo* test systems
^
45
^. No foetal abnormalities were identified in early dysmorphology and reproductive studies in animals
^
45–
47
^.

As the TXA will be delivered at the end of the 3rd trimester of pregnancy when the foetal development is complete, the trial treatment will not have any impact on foetal development.

The foreseeable risks related to the IM route of administration may include pain, redness and bruising at the injection site and a rare risk of infection at the injection site.

The study also involves additional blood samples from all participants. We will take the smallest possible volume of blood that will allow us to carry out the analysis. The total volume of blood taken from the participating women (maximum of 35 mL over 24 hours) should have no clinical impact on the participant. One blood sample (2 × 10 µl) will be taken from the neonate at the time of the routine heel prick test.

We will routinely assess all women for nausea, vomiting, diarrhoea, thrombotic events, seizures and injection site reactions as secondary outcomes. Additionally, all neonates will be routinely assessed for birth complications and adverse events.

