### Baseline data collection

Baseline parameters will be used to build a PK model that describes the TXA concentration in the blood over time following TXA administration. 

The following baseline data will be recorded:

•Demographic (age) and anthropometric data (height and weight [body mass index and body surface area using the Du Bois formula will be derived]). Information on these parameters can be collected at baseline•Medical and pregnancy history•PPH risk factor(s)•CS planned date and time•Reason for CS•Vital signs including blood pressure, temperature, heart rate, and respiratory rate•Full blood count•Blood test to assess renal function (urea, creatinine, estimated glomerular filtration rate)•Any foetal abnormalities•Any foetal distress

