**Maternal:**

**• Blood lost:** Blood lost from incision to 2 hours after the CS will be estimated. The amount of blood in sponges and drapes used in surgery and blood loss from suctioning (excluding amniotic fluid) will be estimated. At the end of surgery, a calibrated obstetric drape will be used for 2 hours. 

**• Reaction at site of IM injections**: Each IM injection site will be inspected for local reactions at the same time as PK blood sampling and then daily thereafter (for 7 days or until prior discharge).

**• Vital signs**: Participants will have their blood pressure, temperature, heart rate and respiratory rate recorded at the time of each PK blood sampling and daily until discharge or day 7.

**• Treatments:** Data on treatments likely to influence PK levels of TXA (blood product transfusion and IV fluids administration, TXA or other antifibrinolytics) will be collected from the time of TXA administration up to the time of the last PK sample.

**• Adverse events:** As described in section “Pharmacovigilance”, will be recorded up to 7 days.

**• Clinical diagnosis of PPH:** Clinical diagnosis of PPH up to 24 hours after birth (total blood loss of >1000 mL, or any blood loss sufficient to cause haemodynamic instability or requires further treatment).

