## Pharmacovigilance

Maternal events which occur as a consequence of the CS, or events which commonly occur in this population independent of exposure to the TXA administration, and those which are study endpoints do not need to be reported as an adverse event. Congenital or genetic abnormalities in neonates do not need to be reported as adverse events as these events are collected routinely. All other events fulfilling the criteria below should be reported. If a participant (both maternal and neonate) develops an adverse event, they should be treated in line with local procedures. In the definition below, participant refers to both maternal and neonate (s).

The flow chart of the safety reporting is shown in Additional file 6 (see
*Extended data*)
^
49
^.

More details on pharmacovigilance are available in Additional file 3 (see
*Extended data*)
^
49
^.

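### Temperature is recorded throughout but not listed for summary, and the count of abnormal vital signs makes no reference to the pre-dose value

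*Protocol article*

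**What the plan says.** Four vital signs are collected. Baseline data collection lists "Vital signs including blood pressure, temperature, heart rate, and respiratory rate". Under Follow-up assessments, the maternal items have "blood pressure, temperature, heart rate and respiratory rate recorded at the time of each PK blood sampling and daily until discharge or day 7".

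The analysis is set out under Safety parameters. The vital-signs paragraph begins "Descriptive statistics for blood pressure, heart, and respiratory rate will be presented in tabular form" and continues "Number (%) of women with abnormal values in each randomised group will be presented". It does not say which signs the second sentence covers, what counts as abnormal, or how the pre-dose value enters.

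The paragraph just before it, on full blood count and renal function, does deal with baseline: "Changes from baseline as well as shift tables for laboratory parameters will be presented".

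Safety of the three routes is a secondary objective. The section on the safety of TXA names, among the foreseeable risks of the IM route, "a rare risk of infection at the injection site".

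**The concern.** Two things do not fit together.

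First, the list of vital signs to be summarised is shorter than the list collected. The missing sign is temperature, which is the systemic sign most closely tied to infection, and injection-site infection is a risk the article itself names.

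Second, the abnormal-value count is silent on the pre-dose value. A woman who was hypertensive or tachycardic before dosing, and remains so, may be counted in the same way as one who becomes so afterwards. The eligibility criteria do not exclude women with abnormal vital signs at baseline. With about 30 women per arm, a handful of pre-existing cases falling unevenly would shift the percentages by an amount that could be mistaken for a difference between routes.

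**Working it through.** **Lists side by side.** The article states no figure on this point, so there is none to reproduce.

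| Sign | Baseline | Follow-up | Listed for descriptive statistics |
|---|---|---|---|
| Blood pressure | yes | yes | yes |
| Heart rate | yes | yes | yes |
| Respiratory rate | yes | yes | yes |
| Temperature | yes | yes | no |

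**Possible size of a chance pre-dose imbalance.** The arm size of 30 comes from the article. It is approximate, because replaced participants' data are also used. The pre-dose abnormality rate *p* is not given, so a range is assumed. For two independent arms, X and Y are each Binomial(30, *p*):

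- expected number abnormal before dosing, per arm: 30*p*
- SD of the difference between two arms in the proportion abnormal: √(2*p*(1−*p*)/30)
- chance that a given TXA arm has at least three more such women than control (3/30 = 10 percentage points): P(X − Y ≥ 3), exact binomial

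| Assumed *p* | Expected per arm | SD of difference | P(at least 3 more) |
|---|---|---|---|
| 5% | 1.5 | 5.6 points | 6.5% |
| 10% | 3 | 7.7 points | 13.7% |
| 20% | 6 | 10.3 points | 20.9% |
| 30% | 9 | 11.8 points | 24.0% |

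**Why the denominator matters.** Suppose 6 of 30 women (20%) in a TXA arm and 3 of 30 (10%) in control are abnormal before dosing. Suppose also that those women stay in the count, and that the same 15% (assumed) of initially normal women become abnormal in both arms. There is then no treatment effect.

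- Any abnormal value, all women: 1 − 0.80 × 0.85 = 32.0% against 1 − 0.90 × 0.85 = 23.5%, an apparent difference of 8.5 points.
- Newly abnormal, over all women: 0.80 × 0.15 = 12.0% against 0.90 × 0.15 = 13.5%, an apparent difference of −1.5 points.
- Newly abnormal, among women normal before dosing: 15% against 15%, a difference of 0.

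Only the last count is free of the pre-dose imbalance.

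**The case against.** A reader might infer that fever will go unreported. The text does not support that.

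- The abnormal-value sentence is not confined to the three named signs. It stands under a vital-signs heading, so it can be read to include temperature.
- Fever can also appear as an adverse event. The Pharmacovigilance section exempts consequences of the caesarean and events common in this population, then says "All other events fulfilling the criteria below should be reported". Those exemptions could remove some postoperative fever, but not all fever.
- Injection sites are inspected at each PK sample and then daily. The number and severity of reactions are reported, and the Data Monitoring Committee reviews them. The local signs of the named IM risk are thus covered directly.

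A reader might also infer that the table would systematically attribute pre-existing abnormality to TXA. Allocation is randomised 1:1:1:1 with a no-TXA arm that serves as the safety control, so pre-dose abnormality is balanced in expectation and only chance imbalance remains. The article does not say that pre-dose readings are counted, and it plans no between-group test of vital signs.

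A third tempting inference is that the present count dilutes a true treatment effect and that counting new cases would restore it. If the emergent rate rises from *e*₀ to *e*₁, the difference in any abnormality is (1−*p*)(*e*₁−*e*₀). The difference in new cases over all randomised women is the same. Only restricting the denominator changes it.

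Finally, baseline handling of a descriptive safety table is often left to a statistical analysis plan, which is not shown. That makes the second half of the point the weaker one. What stands against the objection is that the article fixes a list that disagrees with its own data collection, and that it settles baseline handling for laboratory values but not for vital signs in the next paragraph.

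**Conclusion.** The point holds as a minor one. Temperature is collected at baseline and follow-up but is absent from the signs listed for descriptive statistics, so no temperature summary is planned. This rests on the text alone.

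The abnormal-value count makes no reference to the pre-dose value, so chance imbalance between arms of about 30 can enter the table. Its size rests on assumed pre-dose rates of 5% to 30%, and on pre-existing abnormality either persisting after dosing or being counted from the pre-dose reading. If abnormality resolves and only post-dose readings are counted, the effect is smaller.

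Only descriptive reporting under a secondary safety objective is affected. The primary PK analysis is not.

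**What to change.** In the vital-signs paragraph under Safety parameters:

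1. Add temperature to the signs summarised, and say that the abnormal-value count covers all four.
2. Count women with an abnormal post-dose value among those whose pre-dose value for that sign was normal, and state that denominator in the table. For the no-TXA arm, the baseline value serves as the reference.
3. Show change from the pre-dose value for each sign, as is already done for laboratory values. This also keeps in view any worsening in women who were abnormal at the start and so fall outside the count in step 2.

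The cost is a sentence or two of text and a little programming. No new data, visits or samples are needed.
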